# List of used acronyms and abbreviations

| **Abbreviation** | **Term/Explanation** |
| --- | --- |
| AE | Adverse Event = any untoward medical occurrence |
| AR | Adverse Reaction = adverse event, that is each unfavorable and unexpected reaction to a study treatment, regardless of dose |
| CA | Competent Authorities |
| CI | Confidence interval |
| CIDAMP | Cationic intrinsically disordered antimicrobial peptides |
| CHG | Chlorhexidine gluconat |
| CRF | Case Report Form |
| DSUR | Development Safety Update Report = annual safety report |
| eCRF | Electronic Case Report Form |
| EPM | Etikprövningsmyndigheten (English: Swedish Ethical Review Authority) |
| FLZ | Fluconazole |
| GCP | Good Clinical Practice |
| GDPR | General Data Protection Regulation |
| ICH | International Council for Harmonization |
| IHC | Immunohistochemistry |
| ITT | Intention-to-treat = including all data from all subjects who have participated in the study |
| LVFS | Läkemedelsverkets författningssamling (English: Swedish Medical Products Agency’s statutes) |
| NSAID | Non Steroid Anti-Inflammatory Drug |
| PCR | Polymerase Chain Reaction |
| PP | Per Protocol analysis = including only data from subjects who have completed the study completely in accordance with the protocol, with no deviations from the protocol |
| RCT | Randomized clinical trial |
| RNA | Ribonucleic Acid |
| RVVC | Recurrent vulvovaginal candidiasis |
| SAE | Serious Adverse Event = serious untoward medical occurrence |
| SPC or SmPC | Summary of Product Characteristics |
| SUSAR | Suspected Unexpected Serious Adverse Reaction |

#

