## Primary endpoint (variable)

The proportion of women in each group that has negative vaginal cultures for *Candida albicans* 1 week after active treatment.

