## Overall study design

The study is a 6 months clinical Phase II trial to compare if 1% chlorhexidine gluconate vaginal cream (Hibitane®) is at least as effective and safe as fluconazole (reference treatment) for culture-verified recurrent vulvovaginal candidiasis. The study is a randomized open non-inferiority trial with parallel treatment groups. The trial is not possible to blind for neither participants nor investigators due to the differences between study treatments. There is low risk of bias since the primary outcome variable is objective (negative vaginal culture for *Candida albicans*).

The rational for the study is to find an alternative treatment to fluconazole for RVVC with high tolerability and without cytotoxic effect on epithelial cells and negative impact on the vaginal microbes.

The participants will be randomization to;

- Investigational medication with Hibitane® vaginal cream 8 ml every night for a week and then prophylactic treatment with 8 ml/week for another 11 weeks

or

- Reference treatment with Fluconazole® 150 mg (oral capsule) every 3 days for the first 3 doses, then prophylactic treatment with 150 mg/week for another 11 weeks

Please see section 7 for more details on randomization and study treatments.

Figure 1 Study design

| **Visit** | **1** | **2** | **3** | **4** | **5** |
| --- | --- | --- | --- | --- | --- |
|  |  | CHG | Chlorhexidine gluconate  vaginal application  8 ml/w, 11 w | |  |
|  |  | 8 ml/day,1 w  R |  |  | N=30 |
|  |  |  | Fluconazole  oral capsules  150 mg/w, 11 w | |  |
|  |  | FLZ  150 mg/day,1w |  |  | N=30 |
| **Week:** | **-1** | **0** | **1** | **12** | **24** |
|  | Screening | Inclusion/  Baseline  Randomization | Follow-up | Follow-up | Follow-up and end of treatment |

##

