## Withdrawal criteria

Subjects can discontinue their participation in the study at any time without any consequence to his/her continued treatment. The investigator/sponsor can at any time terminate the study for a subject due to, e.g., unacceptable adverse events/adverse reactions or because the subject does not follow procedures in the study protocol. If the subject discontinues the study, follow-up of this subject will be performed according to the clinic’s routine.

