## Concomitant medications

Medications that are considered necessary for the safety and well-being of the subject can be given at the discretion of the investigator, unless otherwise specified as an exclusion criterion. Concomitant medications are reported in the CRF.

If treatment fails (positive culture for *Candida albicans* and symptoms), rescue medication of vaginal Clotrimazole 200 mg twice per week will be provided in both study groups for the rest of the study period. The regime of Clomitrazole is another established treatment for vulvovaginal *Candida albicans* infection.

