### Drop-outs

Differences in drop-out rates across treatment arms and baseline characteristics will be analyzed using Mann Whitney U test. Efficacy and safety will be analyzed for all randomized patients (i.e. intent-to-treat ITT). Additionally, we will also examine efficacy for the per-protocol (PP) population. We will examine the difference in dropout rates and missing visits across treatment arms.

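### The only per-protocol definition requires a deviation-free 24 weeks, so it removes women from the primary 1-week comparison for events that came after their culture

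*Protocol*

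**What the plan says.** The PP set is defined in one place, the protocol's list of abbreviations: "including only data from subjects who have completed the study completely in accordance with the protocol, with no deviations from the protocol". Section 10.1 (Analysis population) gives numbers per arm and the visit plan, but no PP criteria.

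The length of the study comes from Overall study design: "The study is a 6 months clinical Phase II trial". Visit 5 at week 24 is the last visit. The primary endpoint begins "The proportion of women in each group that has negative vaginal cultures for" *Candida albicans* and is timed 1 week after active treatment, which is Visit 3.

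Section 10.2.2 (Drop-outs) sets the roles of the two sets. The main one is "Efficacy and safety will be analyzed for all randomized patients (i.e. intent-to-treat ITT"), followed by "Additionally, we will also examine efficacy for the per-protocol (PP) population". Section 10.2.1 says the same. Neither section describes a separate PP set for the primary endpoint or limits PP in time.

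**The concern.** Membership of the PP set is settled at week 24, whereas the primary outcome is recorded at Visit 3. Between the two lie the rest of an 11-week prophylactic phase and an observational phase to month 6. A woman who leaves in month 5, skips a prophylactic dose or attends Visit 5 outside its window is no longer a deviation-free completer, so her Visit 3 culture leaves the primary PP analysis. None of those events can have changed that culture.

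If such exclusions were unrelated to the Visit 3 result, the only loss would be precision. A link is plausible, however. The trial is open-label, women may leave at any time, and those still infected have more reason to do so. The protocol also does not say whether a woman given rescue treatment still counts as fully in accordance with it. Selection on the outcome would then enter the PP comparison. In a non-inferiority trial, PP is read beside the intention-to-treat (ITT) result to see whether non-adherence has blurred a real difference. A PP set filtered on post-endpoint events cannot serve that purpose reliably.

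**Working it through.** **1. The plan's own figure.** Section 10.4 gives 86% success in both arms, a margin of 30 points, α = 5%, 90% power, 46 women (23 per arm), and 60 enrolled.

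n per arm = 2 × p(1 − p) × (z₁₋α + z₁₋β)² / Δ²

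- One-sided 5%: 2 × 0.86 × 0.14 × (1.645 + 1.282)² / 0.30² = 22.9, so 23 per arm and 46 in total. This reproduces the plan.
- One-sided 2.5%: 28.1, so 29 per arm and 58 in total. This does not.

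The sample size therefore uses one-sided 5%, while section 10.2.1 speaks of 95% confidence intervals. Results are shown at both levels.

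**2. How exclusion changes the PP rates.** Let p be the true success rate, s the share of successes kept in PP and f the share of failures kept.

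PP success rate = p·s / (p·s + (1 − p)·f); expected PP size = 30 × (p·s + (1 − p)·f)

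Place the truth exactly at the margin: chlorhexidine (CHG) 56%, fluconazole (FLZ) 86%. Suppose 10% of successes and 50% of failures are excluded in both arms:

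- CHG: 0.504 / (0.504 + 0.220) = 69.6%; expected size 30 × 0.724 = 21.7
- FLZ: 0.774 / (0.774 + 0.070) = 91.7%; expected size 30 × 0.844 = 25.3
- PP difference: −22.1 points instead of −30

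**3. False non-inferiority in the PP set alone.** These are exact enumerations with 30 randomised per arm. Non-inferiority is declared if the lower Newcombe limit exceeds −30 points. Every exclusion rate is an assumption, and so is the choice of the Newcombe interval.

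| Excluded from PP | PP rates CHG / FLZ | Difference | Expected n CHG / FLZ | False NI, 95% CI | False NI, one-sided 5% |
|---|---|---|---|---|---|
| None (equals ITT) | 56.0 / 86.0 | −30.0 | 30 / 30 | 2.9% | 5.7% |
| 20% of all women, both arms | 56.0 / 86.0 | −30.0 | 24.0 / 24.0 | 3.2% | 5.9% |
| 10% of successes, 30% of failures, both arms | 62.1 / 88.8 | −26.7 | 24.4 / 26.2 | 5.5% | 9.8% |
| 10% of successes, 50% of failures, both arms | 69.6 / 91.7 | −22.1 | 21.7 / 25.3 | 10.7% | 17.8% |
| 10% of successes, 70% of failures, both arms | 79.2 / 94.9 | −15.6 | 19.1 / 24.5 | 23.3% | 35.7% |
| 50% of CHG failures, 10% of all others | 69.6 / 86.0 | −16.4 | 21.7 / 27.0 | 21.9% | 31.9% |
| 30% of CHG, 10% of FLZ, regardless of outcome | 56.0 / 86.0 | −30.0 | 21.0 / 27.0 | 3.0% | 5.7% |
| 50% of FLZ failures, 10% of all others | 56.0 / 91.7 | −35.7 | 27.0 / 25.3 | 0.9% | 1.9% |
| 40% of CHG successes, 20% of all others | 48.8 / 86.0 | −37.2 | 20.6 / 24.0 | 0.8% | 1.7% |

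The rate rises when failures are lost preferentially at similar rates in both arms, or more on CHG. It barely moves when losses are unrelated to outcome, and it falls under the last two patterns.

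**4. Size of the PP set.** Enrolling 60 for a required 46 allows 1 − 46/60 = 23% loss. With 86% in both arms and one-sided 5%, 23 per arm gives 90% power, 20 gives 86% and 18 gives 83%. A rule that counts any deviation over 24 weeks uses up that allowance faster than one that stops at Visit 3.

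**The case against.** The strongest objection is that PP does not carry the conclusion. Section 10 analyses all randomised women and examines PP additionally; nothing lets PP override ITT. A reader might infer from the table that the trial's own chance of a false non-inferiority finding rises to 11% or 23%. The protocol does not support that reading. If ITT decides, the rate stays at 2.9% under the 95% interval. If both sets had to pass, the rate could not exceed the ITT rate. This part stands in full.

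A second objection is that the direction is assumed. A reader might infer that the PP check leans towards non-inferiority. The last three rows of the table show a neutral pattern and two opposite ones, and the protocol offers no data to choose between them. This also stands.

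Third, treatment failure need not remove a woman from PP. Under Concomitant medications, "rescue medication of vaginal Clotrimazole 200 mg twice per week will be provided in both study groups for the rest of the study period", so rescue alone is not a deviation, and a rescued woman can reach week 24. That weakens one route of selective exclusion. It leaves withdrawal, where "If the subject discontinues the study, follow-up of this subject will be performed according to" the clinic's routine, and any other later deviation.

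Last, the definition sits in a list of abbreviations, and the statistical analysis plan, which is not at hand, may refine it. That limits the weight of the point. Still, it is a stated rule and the protocol's only one, and section 10 uses the term without qualification.

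**Conclusion.** The concern holds in a limited form. As written, the PP definition removes women from the primary comparison for events after their outcome was recorded. This follows from the text and needs no assumption about rates. The consequence is a smaller PP set that can be biased either way. With the truth at the margin and a 95% interval, the PP-only false non-inferiority rate runs from about 1% to about 23% over the patterns tried, against 2.9% without exclusions. That range rests wholly on assumed exclusion rates.

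The ITT error rate is untouched. What suffers is the supporting check: agreement between PP and ITT would reassure less than it appears to, and disagreement would be hard to interpret.

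**What to change.** In the list of abbreviations and in section 10, define PP separately for each endpoint, using only conduct up to that endpoint:

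- Primary endpoint: eligible, active-phase treatment taken as allocated, Visit 3 culture within its window, and no other antifungal before that culture, whatever happens later.
- Month 3 and month 6 cultures: separate sets, each judged on conduct up to its own visit. State whether women who received rescue treatment belong to them.

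The cost is a change of wording and slightly more analysis work. No new data are needed, since compliance is already evaluated at the follow-up visits and in the weekly diary, and visit data are on the case report form. If early exclusions are unrelated to outcome (say 20% in each arm), the PP false non-inferiority rate is 3.2% under the 95% interval, close to the ITT figure.

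Requiring ITT and PP both to show non-inferiority would be a separate decision with a cost in power. This fix does not depend on it.

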# Synopsis

The overall aim of this study is to investigate if vaginally applied 1% chlorhexidine gluconate (CHG) could be an alternative treatment to oral fluconazole (FLZ), both during an acute episode and as prophylaxis, against recurrent infections of vulvovaginal candidiasis (RVVC). If CHG is at least as effective as FLZ with little impact on vaginal lactobacillus, with high tolerability and without cytotoxic effect on epithelial cells, the results of the study might lead to major benefits to the patients with reduced risk of systemic side effects such as drug interactions, development of drug resistance and reduced drug costs.

| EudraCT number:  2020-000758-81 |  |
| --- | --- |
| Title: A RCT for chlorhexidine gluconate as treatment and prophylaxis for Recurrent Vulvovaginal Candidiasis |  |
| Study code: Chlorhex-KKDS-2021 |  |
| Short background/ Rationale/Aim:  Recurrent vulvovaginal candidiasis is common in young fertile women. There are limited treatment options and the recommended treatment of long-term oral fluconazole is not suitable for all patients. The overall aim of this study is to investigate if vaginally applied 1% chlorhexidine gluconate (CHG) is at least as effective as oral fluconazole, both during an acute episode and as prophylactic treatment for recurrent vulvovaginal candidiasis (RVVC). |  |
| Study objectives:  RCT to compare the treatment effect and  safety aspects of vaginal 1%chlorhexidine  gluconate (Hibitane® vaginal cream)  versus oral fluconazole (Fluconazole®)  for recurrent vulvovaginal candidiasis  (RVVC). | Primary objective:  To analyze if vaginal application of CHG is at least as effective as oral FLZ as treatment and prophylaxis of RVVC in terms of clearing the infection (negative culture for *Candida albicans*)  Secondary objectives:  To analyze adverse events  To analyzed clinical symptoms and findings  To study the event of relapses during and after the prophylaxis treatment  To study the effect on vaginal microbiome of lactobacillus before and after treatment and prophylaxis with CHG for RVVC.  To investigate if CHG have toxic effect on the vaginal epithelial cells.  To analyze vaginal biofilm formation before and after treatment and prophylaxis with CHG for RVVC. |
| Study design:  The study is a randomized open Phase II trial and the protocol is designed as a non-inferiority trial. |  |
| Study population:  Women with culture verified recurrent vulvovaginal *Candida albicans* infection |  |
| Number of subjects: 60 |  |
| Inclusion criteria:   - 18-50 years of age - A history of > 2 candida infections the last year - Symptoms of acute vulvovaginal candida infection - Culture verified infection with *Candida albicans* - Adequate contraceptive method - Able to understand oral and written information in Swedish - The subject has given written consent to participate in the study |  |
| Exclusion criteria:   - Severe somatic or mental illness (including liver and renal failure and cardiac disease) - Immunosuppressive medication - Pregnancy - Lactation - Other ongoing gynecological infections - Allergy to fluconazole or Chlorhexidine gluconate - Medication that might have impact on the QT interval (terfenadin, cisaprid, astemizol pimozid, kinidin, erythromycin, halofantrin, amiodaron) - Participation or recent participation (30 days) in a clinical study with an investigational product. Previous participation in this study. | |
| Investigational product(s), dosage, administration:  Chlorhexidine gluconate, 1% vaginal crème (Hibitane®), 8 ml, vaginal application  Fluconazole, oral capsules, 150 mg (control treatment) |  |
| **Study endpoints**:   1. To analyze if vaginal application of CHG is at least as effective as oral FLZ as treatment and prophylaxis of RVVC. 2. To analyze adverse events (AE) 3. To study the effect on vaginal microbiome of lactobacillus before and after treatment and prophylaxis with CHG for RVVC. 4. To study the event of relapses during and after the prophylaxis treatment 5. To investigate if CHG have toxic effect on the vaginal epithelial cells. 6. To analyze vaginal biofilm formation before and after treatment and prophylaxis with CHG for RVVC. | **Primary endpoint**:  The proportion of women in each group  that has cleared the infection after 1week  after treatment, defined as negative  cultures for C. *albicans.*  **Secondary endpoints**:   1. Negative cultures for *Candida albicans* at 3 months’ and 6 months’ follow-ups, after end of prophylactic treatment. 2. Analysis of proportion of women with adverse events (AE). 3. Proportion of women with symptom score > 2 (composite index). 4. Proportion of women with examination score >2 (composite index). 5. Proportion of women with reduced vaginal lactobacilli content in vaginal smears 6. Proportion of women with relapse of *Candida albicans* infection between end of treatment and end of prophylactic treatment (1week post treatment to 3 months’ follow-up) and between 3- and 6 months’ follow-up after end of prophylactic treatment 7. Proportion of women with possible toxic effect on the vaginal epithelium 8. Analysis of biofilm formation during and after treatment and prophylaxis. |
| Study period: | Q2 2021 – Q4 2024 |

# Background and rationale

Vulvovaginal fungal infections are very common, affecting approximately 75% of all women at some point in their lives [1]. Many women relapse and about 5-8% of fertile women suffer from repeated infections, or "recurrent vulvovaginal candida infection" (RVVC), defined as 3-4 infections per year [2, 3]. There are several known risk factors for sporadic fungal infections where antibiotic therapy, pregnancy and immunosuppression are the most common causes. Identified causes of RVVC are on the other hand unclear and the patients are in most cases otherwise healthy. This has prompted theories that the etiology to RVVC could be alterations of the vaginal immune system or specific virulent characteristics of the involved Candida strains [3]. Suffering from RVVC has a major impact on the quality of life of the affected women. For long periods, they cannot have pain free sex and they often suffer from constant irritation and uncomfortableness, which in turn can lead to anxiety, depression and possible development of provoked vestibulodynia [3, 4].

Up to six months of treatment with fluconazole (FLZ) is the recommended treatment for RVVC [5, 6]. Over the last ten years, the use of FLZ has increased markedly in many countries. So far, no major problems have been noted with resistance development, but there is concern that this will occur in the future and alternative treatments are requested [7]. This is one of the reasons why the Swedish Medical Products Agency reintroduced prescription requirements for single dose of FLZ in 2017. Although many patients tolerate the treatment well, there are reported side effects. In recent years, it has emerged that flukonazol interacts with several different types of drugs that are common in the patient group; several antidepressants, pain relief at dysmenorrhea (NSAID) and oral contraceptives to name a few [8]. The most serious interaction is the risk of extended QT range and cardiac arrhythmia. In addition, FLZ is not approved during pregnancy, which in itself poses an increased risk of vulvovaginal fungal infections. [8].

Our research group has previously done an *in vitro* study in which we analyzed the effect of FLZ and the antiseptic substance chlorhexidine gluconate’s (CHG) ability to kill fungal cells and to break down existing biofilm or prevent new biofilm formation [9]. The biofilm formation is an important stage for the fungal cells to attach to surfaces such as skin and mucosa and is considered a first step in the development of an infection [10]. In the biofilm, the fungus can hide from the immune system and also to some extent for various treatments aimed against the fungus. The results of the study showed that CHG was better than FLZ both at killing the fungal cells and preventing new biofilm from forming and dissolving already established "old" biofilm. This effect is absolutely crucial for successful treatment with antimycotics. These encouraging results form the basis of the planned study.

Hibitane® is an over-the-counter vaginal cream consisting of 1% chlorhexidine gluconate with the indication antiseptic use in vaginal examinations, especially during childbirth. The product has been used for a long time in various gynecological and obstetric surgical procedures. Hibitane® is approved during pregnancy and the cream is usually well tolerated [11]. There are only few studies that investigated how vaginal normal flora is affected by CHG. One human study showed a decrease in the number of lactobacilli a week after the vaginal application of 0.5% CHG every night for a week. After 30 days, the vaginal normal flora was basically fully recovered and the side effects were few [12]. In an animal study, no major effect was seen on the vaginal flora after 2 vaginal applications of CGH 0.25% at 24 hours apart [13].

Many women with RVVC are referred to the vulvar clinic at the gynecological department at Danderyd Hospital in Stockholm. We have followed these women clinically for many years and have also performed several scientific studies. Our clinical experience is fully in line with the described high risk of infection relapse and the need for repeated and long use of fluconazole. Several of our patients have problems with side effects of the medication and there are also difficulties in combining fluconazole with other concomittant medications commonly used by this group of patients. If Hibitane® is at least as effective as fluconazole with little impact on vaginal lactobacillus, with high tolerablility and without cytotoxic effect on epithelial cells, the results of the study might lead to that an already established and inexpensive drug can be used by a large group of young women with a new indication.

# Benefit-risk evaluation

In the study we will examine an already approved drug with basically the same indication described in FASS, i.e. antiseptic effect. According to the product recap available for Hibitane® vaginal cream, the only contraindication is contact of active substance with brain or meningeal tissue, or ear canal due to neurotoxicity. Hibitane® is approved for vaginal use even during pregnancy and lactation and is usually tolerated well in the vagina but can provide some skin and mucosal irritation. Allergic reactions are rare. Thereby the possible risks for the patients is considered to be low. The reference treatment is oral fluconazole, which will be used in doses and duration according with administration specified in FASS. There are known AE that could occur during treatment with fluconzole, but the most serious ones are eliminated by the exclusion criteria of the study.

Since vaginal Hibitane® treatment has not been evaluated for vulvovaginal candida infections *in vivo*, there is a risk that the patients will not be optimally treated against their candida infection if Hibitane® turns out to have limited treatment efficacy. However, all patients in the study will have the opportunity for additional follow-ups and optional treatment after the study if they should not recover from the study treatment they have been allocated to.

The gynecological examinations, including vaginal sampling, are conducted according to customary routines. Small (3-4 mm) vaginal biopsies will be taken during the study and may cause some pain associated with the anesthetic, but the biopsy and healing itself should not pose any major risks of bleeding or infection. The research team has previously taken similar biopsies without any complications.

The benefit of the study will mainly be on group level rather than individual benefit. The aim of the study is to be able to offer patients with RVVC an alternative treatment to oral fluconazole. The major long-term benefits for the patients would therefore be reduced risk of systemic side effects and interactions with other medications as well as hampering drug resistance.

Further ethical consideration is handling of patient data. Before entering the study, all patients will sign an orally and written informed consent and receive a study specific code. All the results will be reported on group level and no individual patient will be identified, for more details, please see section 14.

